#### Postintervention Interviews and Focus Groups

Between June and August 2024, qualitative data were collected through interviews and focus groups with teachers, parents, and administrators. These interviews and focus groups gathered insights into teachers’ and parents’ perceptions of the program’s effectiveness, challenges encountered, and suggestions for improving the program. In the intervention group, 5 teachers completed interviews, 4 parents participated in 2 focus groups and 1 parent completed an interview. A total of 4 interviews were conducted with administrators. In the control group, there were 2 interviews with teachers and 3 with parents after the intervention.

The protocols for the qualitative data collection were adapted from protocols used in other qualitative studies of mindfulness programs [75,76]. Modifications were made by the project team to capture a wide range of insights. The protocols for each set of reporters began with questions or probes about experiences with the program (eg, “Describe your experiences working with implementers.”); perceived changes in participants (eg, “Since the program began, what changes, if any, have you observed?”); and experiences with research components (eg, What was your experience with these data collection components?). The wording was modified based on whether the interviewee was a parent, teacher, or administrator. Protocol questions were informed by team members’ foundations in implementation science, addressing broad constructs such as barriers and facilitators of implementation, as well as implementation outcomes such as acceptability or sustainability, more specifically [77,78]. For example, 1 question was, “Thinking about the next academic year, what are your hopes for the programming to continue in your school? What supports will help it continue?”

#### Program Implementation Measures

Several strategies were used to assess implementation fidelity, acceptability, feasibility, and sustainability. In addition to the qualitative interviews, focus groups, and open-ended survey questions about program components (described in the Surveys section and the Postintervention Interviews and Focus Groups section), implementation was documented through (1) implementer-reported fidelity assessment forms, (2) teacher-reported activity logs, (3) attendance and engagement logs, (4) videos, and (5) field notes. Fidelity forms were modified from a previous school-based mindfulness study [76] and included fidelity to curriculum components and core process quality (eg, the day’s planned activities, maintaining engagement, and overall quality). Teacher activity logs documented instances when teachers implemented program activities outside the designated implementation period, including details on which activities were used (eg, weekly primary and booster sessions), how often they were implemented, the duration, and the context in which they occurred. Attendance and engagement logs tracked attendance of children and teachers, as well as engagement, disruptiveness, and open-ended notes per session. Finally, field notes were written per session to document the contextual factors (eg, special considerations for child life events, school disruptions, and technology difficulties).

#### Data Analysis

Qualitative, quantitative, and mixed methods analyses will be used. Scale and subscale reliability was assessed using Cronbach α values. Quantitative data will be analyzed using descriptive and inferential statistics. Standard descriptive statistics are conducted to understand variable distributions (eg, sociodemographic characteristics). Inferential parametric and nonparametric statistics (mean comparisons via 1-tailed *t* tests and linear regression) will be used to answer research questions about program and implementation effects for objectives 2 and 3. Content and thematic analysis approaches will be used to analyze qualitative data (interviews, focus groups, and open-ended survey responses) for objective 1. Qualitative and quantitative findings will be integrated, where appropriate.

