**Objective:**

This pilot randomized controlled trial aims to assess the feasibility and acceptability of implementing MMPs in preschool classrooms and explore their effects on preschoolers’ social-emotional, cognitive, and physiological development. The study also focuses on enhancing prosocial behaviors and reducing problem behaviors. This protocol paper outlines the research procedures, sample demographics, and survey data psychometric properties.

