**Conclusions:**

This paper describes study procedures. Future publications will present primary outcome findings and evaluate the feasibility and acceptability of this MMP and research design in community-based and university-based preschool settings. Future papers will explore the data to provide preliminary evidence for the program’s effectiveness, mechanisms of effects, and the need for larger randomized controlled trials to optimize early childhood mindfulness interventions.

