In response to these gaps, we conducted a pilot RCT to evaluate the hypothesis that MMPs could alter preschoolers’ behavioral difficulties by impacting physiological, social-emotional, and cognitive factors, which, in turn, could affect teacher outcomes. This preliminary evidence will provide support for using these assessments in a future full-scale RCT.

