### Objectives

This pilot study was designed to lay the groundwork for a larger RCT using the MMP and building an evidence base to support broader dissemination of an effective, low-cost, highly scalable program. This pilot study has 3 primary aims.

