#### Effects on Mechanisms and Outcomes

This aim focused on investigating how the implementation of the MMP influences self-regulatory capacities, SEL skills, problem behaviors, and prosocial behaviors, as well as identifying underlying physiological mechanisms of program effects at the midpoint, postintervention time point, and 2-month follow-up. Physiological data were collected after each MMP component, allowing for the evaluation of the effects of sequential implementation on physiological responses.

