## Discussion

### Program Outcomes

The study investigates the effect of an MMP on preschool children’s social-emotional, behavioral, and cognitive outcomes, including effects on acute and chronic stress. A mixed methods approach was used, integrating quantitative, qualitative, and physiological data. The study addresses several notable gaps in the literature, including determining MMP effects on a sociodemographically diverse population of preschoolers, identifying differential responses by program component (eg, movement alone and movement plus breathing), and exploring underlying physiological and social-emotional mechanisms of intervention responsivity. Taking this approach will further enrich our understanding of the potential mechanisms and efficacy of mindfulness-based interventions.

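### Primary outcome findings are promised, but no primary outcome, reporter or contrast is designated, and one-sided tests are planned across aims 2 and 3 under wording that alternates between exploring and determining effects

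*Protocol article*

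**What the plan says.** All references are to the Protocol article.

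- **Primary status.** The abstract's Conclusions state: "Future publications will present primary outcome findings and evaluate the feasibility and acceptability of this MMP and research design". The Objectives section states "This pilot study has 3 primary aims": feasibility, effects on mechanisms and outcomes, and teacher effects. No outcome variable is called primary anywhere.
- **Scope of aim 2.** The section on Effects on Mechanisms and Outcomes lists self-regulation, social-emotional skills, problem behaviors and prosocial behaviors without ranking them, "as well as identifying underlying physiological mechanisms of program effects at the midpoint, postintervention time point, and 2-month follow-up".
- **Reporters.** The Strengths and Difficulties Questionnaire (SDQ) and the Children's Behavior Questionnaire (CBQ) are completed by parents and by lead teachers. Neither is preferred.
- **Analysis.** The Data Analysis section says that mean comparisons by one-sided t test, and linear regression, "will be used to answer research questions about program and implementation effects for objectives 2 and 3". It names no outcome, reporter, time point or contrast, and gives no significance level.
- **Status of the effect analyses.** The abstract's Objective says the trial will "explore their effects on preschoolers’ social-emotional, cognitive, and physiological development". The Background says "we conducted a pilot RCT to evaluate the hypothesis that MMPs could alter" behavioral difficulties. Randomization Procedures gives judging the program's effectiveness as the reason for a comparison group. The Discussion (Program Outcomes) lists "determining MMP effects on a sociodemographically diverse population of preschoolers" among the gaps addressed.

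**The concern.** A reader told to expect primary outcome findings cannot tell from the protocol which result that will be. Two choices matter most here.

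**Reporter.** The Background hypothesis concerns behavioral difficulties. The natural measure, the SDQ total, exists in a parent and a teacher version. Lead teachers rate children in their own classroom, and the control arm is one classroom, so rater and arm are tied together on teacher scores. Parent scores do not share that structure.

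**Contrast.** A mean comparison could be between arms at postintervention, before versus after within the intervention arm, or second baseline versus post within the waitlist arm. Within-arm change over 16 weeks includes ordinary development at ages 3 to 5. At the 2-month point the waitlist children have already received the program.

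If these choices are made after the results are seen, the headline effect can be the most favorable of many. The article says the findings will guide scaling of the trial.

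**Working it through.** The article states no sample size calculation, power or alpha, so there is no figure of its own to reproduce. The check is a count of candidate scores followed by a false-positive rate under stated assumptions.

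**Step 1: count the child scores at one time point** (postintervention, where all are collected).

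- Behavioral tasks: pencil tapping 1, gift delay 2, tower 3, go/no-go 1 = 7
- Teacher report: expulsion risk 5 (full scale and 4 subscales), relationship scale 2, CBQ 3, SDQ 6 (5 subscales and total) = 16
- Parent report: CBQ 3, SDQ 6 = 9
- Hair hormones: 3
- Heart rate variability (HRV): respiratory sinus arrhythmia and vagal efficiency = 2

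Upper count: 7 + 16 + 9 + 3 + 2 = 37.

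The Biomarkers overview presents the 5 biomarker scores as mechanisms. Teacher Reports on the Children describes the expulsion risk measure as one of implicit bias and the relationship scale as one of the teacher's perception (5 + 2 = 7 scores). Two SDQ totals are sums of subscales already counted. Lower count: 37 − 5 − 7 − 2 = 23.

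**Step 2: chance of at least one false positive.** Assume no true effects, k tests, one-sided level α, and equal pairwise correlation ρ between normal test statistics. With z = Φ⁻¹(1 − α):

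rate = 1 − ∫ φ(x) · Φ((z − √ρ·x)/√(1 − ρ))^k dx

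At ρ = 0 this is 1 − (1 − α)^k. For example, 1 − 0.95^37 = 0.850 and 1 − 0.975^23 = 0.441.

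| k | α (assumed) | ρ = 0 | ρ = 0.5 | ρ = 0.8 |
|---|---|---|---|---|
| 37 | 0.05 | 0.850 | 0.427 | 0.226 |
| 23 | 0.05 | 0.693 | 0.359 | 0.198 |
| 37 | 0.025 | 0.608 | 0.279 | 0.137 |
| 23 | 0.025 | 0.441 | 0.225 | 0.117 |

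The expected number of false positives runs from 23 × 0.025 = 0.58 to 37 × 0.05 = 1.85.

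**Step 3: cross-check.** Simulated one-sided pooled t tests with 22 versus 10 children, 37 scores, ρ = 0.5 and no classroom effect gave 0.437 at 0.05 and 0.285 at 0.025, against 0.427 and 0.279 above.

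**Step 4: the reporter choice alone.** For two versions of one total (k = 2, ρ = 0.5) the rate is 0.088 at 0.05 and 0.045 at 0.025, about 1.8 times the assumed level in each case.

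Further time points, and splitting HRV by task, reactivity or recovery, would add tests. They are not counted.

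**The case against.** **The study is a pilot with exploratory wording.** The abstract speaks of exploring the data for preliminary evidence. The Background follows its hypothesis with a sentence calling the evidence preliminary. The Limitations acknowledge the small sample, and the closing Conclusions defer to an adequately powered trial. This stands and lowers the stakes. It does not identify the promised primary outcome, and the exploratory label is not kept consistently.

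**Much detail may sit elsewhere.** Alpha, multiplicity rules and testing order are commonly left to an analysis plan, which is not shown. This also stands, so the absence of a multiplicity rule is not held against the article. Which outcome is primary is protocol content, and this article has a full Outcome Measures section and promises primary findings.

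**A stronger reading is tempting:** that all 37 child scores will be tested at full one-sided alpha and that any of them could be reported as the program effect. The document does not support that. It states no alpha, does not say that every score will be tested or claimed, and assigns some of the 37 roles other than child outcome.

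**The contrast is partly implied.** Randomization Procedures treats the waitlist as the comparison group, and Waitlist Control Procedures ties its own 8-week phase to dosage. That is fair, but the Data Analysis section never fixes it. Nor can one say that the candidate contrasts would disagree, since no outcome data are shown.

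**Naming one score would not make it interpretable as a program effect** with one control classroom and site 2 assigned without randomization. This stands, and it favors estimation over significance claims.

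**Conclusion.** The point holds as an internal inconsistency with a practical consequence. Primary outcome findings are promised and all three aims are called primary, but no outcome, reporter or contrast is designated. One-sided tests are assigned to aims 2 and 3 as a whole, and the text wavers between exploring effects and determining them.

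At an assumed correlation of 0.5, the chance of at least one false positive at one time point is about 0.36 to 0.43 at one-sided 0.05 and 0.23 to 0.28 at 0.025. The range is about 0.12 to 0.85 across both levels, 23 to 37 scores and correlations 0.8 to 0. The value 0.85 is an independence bound, which correlated scores will not reach. These figures assume unadjusted tests, a common correlation and no classroom effect. They show the size of the opening, not what the investigators will do with it. The pilot framing makes this something that should be corrected rather than a fatal flaw.

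**What to change.** The section on Demographics and Study Flow says that data are still being processed, so the following can be recorded before outcome analysis.

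1. State that feasibility and acceptability is the primary aim, with the 75% parent consent target given under Feasibility and Acceptability. The consent results are already reported there, so this cannot be presented as a blind choice for that target.
2. State that all aim 2 and aim 3 effect analyses are exploratory. Report them as estimates with two-sided 95% confidence intervals and without significance claims, in place of one-sided tests.
3. Fix the main child contrast as intervention versus waitlist at postintervention, adjusted for the baseline score and for age. The arms differ in mean age (4.6 versus 3.9 years, P=.006).
4. If one efficacy outcome is to be called primary, name it and its reporter now. SDQ total difficulties would match the Background hypothesis. Which reporter to use is for the sponsor to decide and justify: baseline Cronbach α is 0.81 for parents and 0.87 for teachers, and does not settle it. Otherwise, remove the reference to primary outcome findings from the abstract.
5. Bring the wording in Randomization Procedures and Program Outcomes into line with the exploratory status.

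The cost is wording only, with no new data. The downside is that individual child outcomes can no longer be claimed as significant.

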### Ethical Considerations

All procedures performed in studies involving human participants were in accordance with the ethical standards of the institutional or national research committee and with the 1964 Helsinki Declaration and its later amendments or comparable ethical standards. The study was approved by the University of Illinois Urbana-Champaign Institutional Review Board (IRB23-0310). All data have been deidentified with unique numeric study IDs created for each participant. Digital copies of data are stored on university-maintained secure servers and password-protected computers. Hard copies of data are stored in locked file cabinets in a secure office. Pseudonyms will be used for qualitative data reporting. Audio files, video files, and photos will be destroyed at the end of the study.

Informed consent for children was obtained from legal guardians, and teachers provided consent for their own participation. Participants had the option to provide consent in person or electronically via the Qualtrics survey platform.

Participants were compensated US $5 for each survey they completed. Those who consented to hair collection and wearable sensors received US $10 for each sample. Parents who consented to provide existing school and observational data received US $10. A bonus of US $15 was given to teachers and parents who provided all data at each time point. Participants who completed interviews or focus groups received US $15. The maximum total for parents and teachers was US $100. Teachers who completed the entire study received a US $150 account transfer to purchase supplies for their classrooms.

## Results

### Demographics and Study Flow of Participants

The intervention and data collection have been completed. Currently, data are being processed for analysis. To determine whether there were group differences in demographic variables between the intervention and waitlist control groups, we conducted *t* tests for continuous variables and chi-square tests (Fisher exact test) for categorical variables. The intervention group was significantly older than the control group (t_30_=−2.97; *P*=.006). There were no other statistical differences in any demographic characteristics.

Overall, there was limited attrition across the study. The study flow and sample sizes for each component are illustrated in Figure 2.

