## Abstract

**Background:**

Chronic stress and emotional and cognitive regulation difficulties during early childhood are associated with risky behaviors and negative outcomes later in life. As preschoolers are at a developmental stage where their emotional and cognitive regulation skills are still emerging, they often rely on external support to manage their emotions and behaviors. Intervening early promotes healthy development and preventing adverse outcomes. Mindful movement practices (MMPs)—which incorporate physical activities, breathwork, and reflective exercises—show the potential to enhance emotional and behavioral skill regulation. However, the impact of MMPs on cognitive and social-emotional development in young children has not been thoroughly researched, and the underlying mechanisms remain unclear.

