### Participants

A total of 40 participants were enrolled in the RCT part of the study. Participants included 32 preschool children aged 3 to 5 (mean 4.4, SD 0.64) years: 17 (53%) female, 11 (34%) Black, and 4 (12%) Hispanic. Demographics of children were based on parent reports unless those data were missing (n=3, 9%), in which case teacher-reported values were used. In total, 69% (22/32) of the children received the intervention immediately, and 31% (10/32) were assigned to the waitlist control group. Of the 40 participants enrolled across the 3 classrooms, 8 were female teachers with a mean age of 37.9 (SD 11.47) years: 3 (38%) were Black and 4 (50%) were White. A total of 29 parents with a mean age of 33.6 (SD 6.75) years completed the demographic questions: 23 (79%) female, 12 (41%) Black, and 2 (7%) Hispanic. Baseline demographics by intervention group for children and parents are presented in Tables 1 and 2.

**Table 1 table1:** Demographic characteristics of children (N=32).

Characteristics		Full sample	Intervention (n=22)	Control (n=10)
Age (y), mean (SD)		4.4 (0.64)	4.6 (0.50)	3.9 (0.72)

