#### Data Collection Timeline

Data were collected at 4 time points: baseline (preintervention; all classrooms), midintervention time point (8 weeks into programming; all classrooms), postintervention time point (immediately following the 16-week intervention or waitlist period; all classrooms), and 2-month follow-up (2 months after the intervention; 1 intervention classroom). In the waitlist control group, the postintervention time point also served as their second baseline and the 2-month follow-up served as their postintervention time point (immediately after the 8-week intervention). The data collection time points are illustrated in Figure 1 for the intervention (black) and waitlist control (gray) groups. At each time point, survey data were collected electronically (in person or online) or via paper and pencil, whichever was feasible and preferred by participants. Behavioral assessments were administered at all time points except for the midintervention time point.

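### Program effects are to be tested by 1-tailed t tests and linear regression with neither tied to age or baseline, although the intervention children are about 1.1 to 1.2 SD older

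*Protocol article*

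**What the plan says.** Data Analysis gives the inferential methods for objectives 2 and 3 in one sentence: "mean comparisons via 1-tailed *t* tests and linear regression) will be used to answer research questions about program and implementation effects". Both methods are listed. Neither is called primary, no covariate is named, and the score to be compared (post or change) is not given.

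Demographics and Study Flow of Participants reports that "The intervention group was significantly older than the control group" (t on 30 df = −2.97, P = .006). Table 1 gives mean ages of 4.6 (SD 0.50) for 22 intervention children and 3.9 (SD 0.72) for 10 controls. No analytic response is attached to the finding, and Limitations does not mention it.

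Baseline values exist. Data Collection Timeline states: "Data were collected at 4 time points: baseline (preintervention; all classrooms". For the child tasks it adds: "Behavioral assessments were administered at all time points except for the midintervention time point".

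Randomization Procedures explains that two site 1 classrooms were allocated by drawing lots and the single site 2 classroom was assigned to the intervention. There is therefore one control classroom.

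**The concern.** The article itself gives the reason to expect age to matter: its Background says that "preschoolers are at a developmental stage where their emotional and cognitive regulation skills are still emerging". The pencil tapping, go/no-go, gift delay and tower tasks measure such skills. If older children score better, an intervention arm that is 0.7 years older starts ahead, and a comparison of post scores by arm counts that head start as program effect. A 1-tailed test puts the resulting error on the side that favors the program.

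Randomization offers little protection, because only one pair of classrooms was drawn by lot. The results are meant to give preliminary evidence of effectiveness and to guide a larger trial, so an inflated difference could carry into that planning.

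**Working it through.** **1. Reproduce the reported age test.** Inputs from Table 1: 4.6 (0.50), n = 22; 3.9 (0.72), n = 10.

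- Pooled SD = √[(21 × 0.50² + 9 × 0.72²)/30] = √[(5.25 + 4.67)/30] = 0.575.
- t = (3.9 − 4.6)/(0.575 × √(1/22 + 1/10)) = −3.19, P = .003.
- Over the rounding range of the printed means and SDs, t runs from −2.71 to −3.68, which contains the reported −2.97.
- t = 2.97 on 30 df gives two-sided P = .0058, matching the reported .006.

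The reported test is consistent with Table 1.

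**2. Size of the age gap.**

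- From the reported t: 2.97 × √(1/22 + 1/10) = 1.13 SD.
- From Table 1: 0.7/0.575 = 1.22 SD.
- On the full-sample SD: 0.7/0.64 = 1.09 SD.

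**3. Consequence for a t test on post scores.** The article gives neither a significance level nor an age-outcome correlation. Assume a nominal 5% level, no true program effect, an outcome that improves with age, and a within-arm correlation r. The spurious shift is r × 1.13 SD. The noncentrality is r × 1.13 × √(22 × 10/32) = r × 2.97, on 30 df.

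| r (assumed) | Spurious shift (SD) | 1-tailed error | 2-tailed error |
|---|---|---|---|
| 0.1 | 0.11 | 8.8% | 6.0% |
| 0.2 | 0.23 | 14.4% | 8.9% |
| 0.3 | 0.34 | 21.9% | 13.9% |
| 0.4 | 0.45 | 31.4% | 21.0% |
| 0.5 | 0.57 | 42.3% | 30.1% |

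**4. Which analyses remove it.** Simulation under no effect: 22 and 10 children, age gap fixed at 1.13 SD, assumed pre-post correlation 0.6, the same age effect at both times, 6,000 runs per row. Entries are 1-tailed error rates.

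| r | Post t test | Change t test | Arm + baseline | Arm + age | Arm + age + baseline |
|---|---|---|---|---|---|
| 0.2 | 14.1% | 4.9% | 8.9% | 5.1% | 5.0% |
| 0.3 | 20.2% | 5.3% | 11.4% | 5.0% | 5.1% |
| 0.4 | 30.5% | 5.0% | 13.3% | 5.1% | 4.8% |
| 0.5 | 40.6% | 4.9% | 16.9% | 5.2% | 4.9% |

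Baseline alone is not enough; age has to be in the model. The change-score result depends on the age effect being equal at both times.

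**5. Price in precision.**

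- R² of arm on age = 2.97²/(2.97² + 30) = 8.82/38.82 = 0.227.
- Variance inflation = 1/(1 − 0.227) = 1.29, so the SE is multiplied by √1.29 = 1.14.
- With an assumed pre-post correlation of 0.6, baseline multiplies the SE by √(1 − 0.36) = 0.80.
- Net: 1.14 × 0.80 = 0.91 of the unadjusted SE, as an approximation.

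**The case against.** The strongest reply is that linear regression stands in the same sentence as the t tests, that age and baseline may enter it, and that an article may leave its covariate list to a fuller plan. This is right as far as it goes, and a missing covariate list alone would not be a finding. What remains is that the article commits to 1-tailed mean comparisons for program effects alongside its own report of a large age gap, and does not say which method carries the conclusion.

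A reader might infer that an unadjusted t test is the lead analysis and that age differences will be read as program effects. The documents do not support that. Neither method is ranked, the word unadjusted does not appear, and change scores fit the text as well as post scores. The bias is a risk under one permitted reading.

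A reader might also infer that leaving out baseline throws away most of the precision. Step 5 does not bear this out: the net gain is about 9% in SE, and only under an assumed correlation.

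Three further limits stand. The size depends on a correlation that the article does not give, and at 0.1 it is small. The argument concerns child outcomes that change with age, so it does not reach teacher self-reports and may have little force for some biomarkers. Finally, this is a pilot that explores effects and defers firm conclusions to a larger trial, which lowers the stakes.

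**Conclusion.** The concern holds as a defect in how the analysis is fixed. The arms differ in age by 1.13 SD (from the reported t) to 1.22 SD (from Table 1), the authors knew this, baseline scores are on file, and the stated methods allow a 1-tailed t test on post scores that takes account of neither.

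Used on an age-related child outcome, that test may show a spurious benefit of 0.11 to 0.57 SD and an error rate of about 9% to 42% in place of 5%. These ranges assume no true effect, a one-sided 5% level and within-arm age-outcome correlations of 0.1 to 0.5. Regression on arm, age and baseline brings the error back to about 5% under the simulated conditions. It does not cure the confounding of age with classroom and site, because there is only one control classroom.

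**What to change.** State the following before the child outcomes are analyzed:

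- For each child outcome measured before and after, the main analysis is the already planned linear regression of the post score on arm, baseline score and age in years as a continuous variable. Use an ordinal or other suitable model for short ordinal scores, such as the 1 to 5 gift delay score and the 0 to 2 turn-taking score.
- t tests and unadjusted means are descriptive only.
- Limitations reports the age imbalance and says that adjustment cannot separate age from classroom or site with a single control classroom.

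No new data are needed. The cost is 2 degrees of freedom and an SE inflation of about 1.14 from including age. A predictive baseline offsets this (net about 0.91 at an assumed pre-post correlation of 0.6); if baseline predicts poorly, most of the inflation stays. The cost weighs more where fewer than 32 children contribute, as with hair samples.

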**Disability, n (%)**				
	None	27 (84)	17 (77)	10 (100)
	One or more disabilities	5 (16)	5 (23)	0 (0)

^a^Samples sizes of <5 participants.

**Table 2 table2:** Demographic characteristics of parents (N=29).

Characteristics			Full sample		Intervention (n=19)		Control (n=10)
Age (y), mean (SD)			33.6 (6.75)		34.8 (5.64)		30.9 (8.36)
Number of children, mean (SD)			2.1 (1.11)		2.0 (0.77)		2.4 (1.57)

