**Race, n (%)**							
	Asian, Native Hawaiian, Other Pacific Islander	—		—		—	
	Black or African American	12 (41)		5 (26)		7 (70)	
	White	13 (45)		10 (53)		—	

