**Income range (US $), n (%)**							
	≤$26,000	8 (28)		6 (32)		—	
	$27,000 to $49,000	12 (41)		5 (26)		7 (70)	
	≥$50,000	7 (24)		7 (37)		—	

^a^Samples sizes of <5 participants, except for reported missingness.

^b^GED: General Educational Development.

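### The statement that the arms differ demographically only in child age conflicts with Table 2, where parent income and marital status differ at P<.05 and parent race is borderline

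*Protocol article*

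**What the plan says.** In the Results, under Demographics and Study Flow of Participants, the article describes t tests for continuous variables and "chi-square tests (Fisher exact test) for categorical variables". It then states "The intervention group was significantly older than the control group" (t with 30 df = −2.97, P=.006) and concludes "There were no other statistical differences in any demographic characteristics".

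The Participants section sets the scope: "Baseline demographics by intervention group for children and parents are presented in Tables 1 and 2". Table 2 covers 29 parents, 19 intervention and 10 control. Small cells are replaced by a dash, explained as "Samples sizes of <5 participants, except for reported missingness".

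Randomization Procedures says that the two site 1 classrooms were drawn by lot, whereas the single university classroom was assigned to the intervention. Data Analysis plans t tests and linear regression for program effects. Limitations does not mention baseline imbalance.

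**The concern.** The sentence reports completed tests, so it can be checked against the counts printed in the same article. Several parent rows in Table 2 look far apart: married 74% of the intervention arm against at most 4 of 10 controls, Black 26% against 70%, and no control parent left for the top income band after subtraction.

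The outcome data are still being processed. A reader told that age is the only difference would think of adjusting for age alone and would treat the arms as otherwise comparable. The allocation gives no general protection here, because one of the two intervention classrooms was not randomised. Part of the child behaviour data is also rated by the parents whose circumstances differ.

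**Working it through.** **Level and sidedness.** Neither is stated for these comparisons. A t of −2.97 on 30 df has two-sided P=.0058, which matches the printed .006, so two-sided tests at .05 are assumed. The rounded means and SDs in Table 1 (4.6, SD 0.50, n=22; 3.9, SD 0.72, n=10) give |t|=3.19. Rounding allows 2.71 to 3.68, so the age result reproduces.

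**Recovering the control cells (Table 2; full sample minus intervention).**

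| Row | Full | Intervention | Control |
|---|---|---|---|
| Income, lowest band | 8 | 6 | 8−6=2 |
| Income, middle band | 12 | 5 | 7 (printed) |
| Income, highest band | 7 | 7 | 7−7=0 |
| Income not shown | 29−27=2 | 19−18=1 | 10−9=1 |
| Married | 16 | 14 | 16−14=2 |
| Black parents | 12 | 5 | 7 (printed) |
| White parents | 13 | 10 | 13−10=3 |

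**Income.** Expected counts are row total × arm total / 27, with 18 intervention and 9 control parents classified: 5.33/2.67, 8/4 and 4.67/2.33. The sum of (observed−expected)²/expected is 0.083+0.167+1.125+2.250+1.167+2.333 = 7.125 on 2 df, P=.028. The exact (Freeman-Halton) test gives P=.024. With the two unclassified parents as a fourth row (1 versus 1), exact P=.048 and chi-square P=.065.

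**Marital status.** Married versus all others is 14/5 against 2/8. Chi-square is 7.63 on 1 df, P=.006; with continuity correction P=.018; Fisher P=.016. In the four-row table, two rows are wholly suppressed and the single-parent row (6 in total) is suppressed by arm. All fill-ins compatible with the under-5 rule were enumerated:

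| Parents missing | Compatible tables | Chi-square P | Exact P |
|---|---|---|---|
| 0 | 18 | .0015 to .047 | .0008 to .023 |
| 1 | 43 | up to .072 (7 above .05) | up to .035 (none above .05) |
| 2 | 62 | up to .12 (8 above .05) | up to .072 (4 above .05) |

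**Parent race.**

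| Grouping | Chi-square P | Corrected P | Exact P |
|---|---|---|---|
| Black versus all others (5/14 against 7/3) | .023 | .061 | .046 |
| Three rows, suppressed row taken as 4 versus 0 | .053 | – | .048 |
| Black versus White only | .072 | .16 | .11 |

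If fewer than 4 parents belong to the suppressed row and the rest are missing, the exact P is .11 to .14.

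**Does one consistent choice of test rescue the sentence?** Exact tests throughout flag income and marital status, and race narrowly. Uncorrected chi-square throughout flags income among classified parents and married versus not. It also flags parent sex and employment (.046 each), parent ethnicity (.043) and child ethnicity (.044), all of which exceed .05 under Fisher (.068, .068, .11 and .079).

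**Direction of the income difference.** The lowest band holds 6/19 (32%) of intervention and 2/10 (20%) of control parents. The highest holds 7/19 (37%) and 0/10. All 6 unemployed parents are in the intervention arm. A rank test across the three bands gives P=.41.

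**The case against.** The strongest defence is scope. The sentence follows directly on a child-only result, and for the child variables it is true under Fisher: ethnicity .079, disability .16, sex .27, race .48, language .70. But the sentence says any demographic characteristic, and the article introduces both tables as baseline demographics by group. The child-only reading would itself need a change of wording.

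A second defence is the treatment of missing data. It has some force. Income passes .05 on chi-square (.065) if missing is made a category, and the four-row marital result is not fixed by the printed margins once a parent or two is missing. Making missing a category is not the usual analysis, however, and most compatible marital tables with up to two missing remain below .05.

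Multiplicity does not help. No adjustment is mentioned, and Bonferroni over the 15 variables in Tables 1 and 2 (.05/15=.0033) would also remove the age difference that the article reports as significant.

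Two stronger readings should be resisted. A reader might infer that parent race clearly differs as well. It does so only under some tests and groupings, and the three-row result rests on a suppressed cell. A reader might also infer that the intervention arm is simply better off because the university site was placed there. The Setting section does describe site 1 families as 90% low-income and site 2 as about 20% to 30%. But the intervention parents are over-represented at both ends of the income range, the rank test shows no shift, and no demographics are given by site.

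**Conclusion.** The sentence is wrong as written. Income differs under both named tests (exact .024, chi-square .028) among the 27 classified parents, with every cell fixed by subtraction. Marital status differs as married versus not (.006 to .018), and over four categories for every fill-in with no missing parents. That four-category result is not guaranteed if one parent (chi-square) or two (exact) are missing. Parent race is a large but borderline difference.

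This rests on two-sided tests at .05, on the sentence covering both tables, and, for income, on leaving out the two unclassified parents. It does not show that any outcome comparison is biased, or how much of the imbalance comes from site. Nor would non-significance with 10 controls have shown balance.

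**What to change.** Rewrite the sentence to report parent income and marital status as differing between arms and parent race as borderline. State for each row which test was used and how many values are missing. Because the one university classroom was assigned to the intervention without randomisation, do not describe the arms as comparable apart from age.

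Wherever an arm effect is reported, add an income-adjusted sensitivity analysis, labelled exploratory given n=32. It should note that no control parent is in the highest band, so adjustment there depends on the model, and that it cannot separate arm from site or classroom.

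The cost is a few lines of text and some added table entries, a less favourable statement of comparability, and somewhat less precise adjusted estimates.
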